## Study population

8

### Study population

8.1

The study is conducted among male and female patients older than 18 years old, who signed the informed consent form with diagnosed primary colon cancer T1‐4a N0‐2 M0‐1 (in case of resectable metastases). All patients should meet all inclusion criteria and have no exclusion criteria.

### Inclusion criteria

8.2

Histologically confirmed adenocarcinoma of the colon (caecum, ascending, hepatic flexure, transverse colon, splenic flexure, descending colon, sigmoid).TNM stage according to VII version T1‐4aN0‐2 M0‐1 (M1 in case of resectable metastases (see 10·2) confirmed by preoperative staging (colonoscopy, CT chest and abdomen).Clinical indications for colonic resection.ECOG status – 0‐2.Age above 18 years old.Signed informed consent.

### Exclusion criteria

8.3

Medical or psychiatric reasons interfering with patient's decision to participate in the study.Pregnancy or breastfeeding.Medical conditions contraindicating surgical procedure.Synchronous or metachronous malignancies.Invasion to adjacent organs.Non‐resectable metastases.Acute bowel obstruction, bleeding or perforation.Indications for isolated transverse colon resection.Neoadjuvant chemotherapy.

## Quality control

9

### Centre registration

9.1

Centre registration procedure is initiated after centre principal investigator's application. Not less than 50 colonic resections for cancer are to be performed annually in the centre. Conditions to perform staging, treatment, morphological assessment and follow‐up according to current protocol are required. Local ethical committee approval is needed.

### Surgeon registration

9.2

To participate in the study a surgeon should have an experience of not less than 20 D3 and 20 D2 lymph node dissection procedures for colon cancer. Surgeons are separately registered for open and laparoscopic procedures. Unedited videos of surgical procedures are required for right hemicolectomy and left (or sigmoid) hemicolectomy – two for each with D2 and D3 lymph node dissections (video assessment can be omitted if coordinating investigator of the study observed mentioned amount of procedures in person). After revision of the application additional videos may be required for assessment by coordinating investigator or a designated expert. Key points for assessment of surgical quality include, but are not limited by the principles noted in *Appendix*
S1 (supporting information). Registered for the study surgeon should be scrubbed and take part in the procedure from the beginning of mobilization to the end of anastomosis formation. Participation of the registered surgeon as an assistant is possible. Presence of the registered surgeon in the operating room not being in the scrubbed team is not allowed.

### Quality of surgical procedures control

9.3

To provide routine quality control in every centre photographs of each procedure are required to assess the lymph node dissection level and vessels ligation – for instance, photos containing vessels with a clip prior to transection.

### Morphological assessment

9.4

Groups of lymph nodes are to be marked on a non‐fixed specimen by a member of the surgical team taking part in the procedure determined by the registered surgeon. Groups are marked according to performed dissection level using Japanese classification (*Fig*. 1, *Appendix*
S1, supporting information). Proximal part of 252 group between left colic and first sigmoid artery is marked as 252A and the part between the first sigmoid and 251 group is marked as 252B.

Specimen assessment is performed using principles, described by N. West et al.^12^ Full protocol of pathology assessment is described in *Appendix*
S2 (supporting information).

## Patient treatment

10

### Preoperative care

10.1

Preoperative investigations and co‐morbidities treatment is performed according to centre's guidelines and protocols. Preoperative staging is to include, but not limited to IV contrast CT chest and abdomen (or abdominal MRI if CT is contraindicated), colonoscopy, histological confirmation of cancer, cancer embryonic antigen level.

If a female patient is not in menopause or it has been less, than 2 years after menopause, a pregnancy test is performed. Results of investigations and conclusion if a patient meets eligibility criteria are documents in case report file.

If a treatment of co‐morbidities is required prior to surgery it is performed before the patient is included.

### Patient enrolment

10.2

Patients are enrolled by investigating physician. Study is discussed with the patient and time and opportunity is given for the patient to familiarize with the informed consent. Patient's consent is confirmed with the signature. After informed consent is signed patient is considered as included in the trial.

For patients with resectable metastases before enrolment treatment plan of metastases removal should be formulated and documented (simultaneous operation or staged procedures). If metastases cannot be resected, such patients are not included in the trial.

Patients meeting all inclusion criteria and having no exclusion criteria are randomized for D2 or D3 lymph node dissection (see 7·2).

### Surgery

10.3

Surgical operation is performed under general anaesthesia with or without spinal or epidural. During screening a registered surgeon determines necessary extent of colonic resection and planned approach in accordance with the type of surgery for which the surgeon was registered. Vessels, which are to be ligated according to tumour location, are documented. These vessels are to be dissected in D2 or D3 area depending on randomization group. Randomization group does not interfere with colonic resection extent, but only determines the area of ligation of vessels mentioned before randomization. Steps of surgery and extent of lymph node dissection are described in *Appendix*
S1 (supporting information).

Date of surgery, time of start and end of surgery, blood loss, blood transfusions and approach are registered. In case of conversion, reason of conversion is noted: “tactical” conversion is performed after laparoscopic revision in case of new data, complicating laparoscopic procedure (adhesions, tumour size etc.), “reactive” conversion is understood as a change in approach because of intraoperative events (bleeding, perforation etc.). Intraoperative findings, main steps and type of surgery are registered in operative notes and in electronic CRF (eCRF). In case of multiorgan resections the extent and details of other organ resections are documented.

Surgeon's impression on performed extent of lymph node dissection, quality of CME and quality of surgery in general is registered noting if lymph node dissection was compliant with the randomization group. Photos of ligated vessels prior to transection are attached. If performed lymph node dissection differed from the randomization group, reason is explained.

Surgical wound closure details are documented.

### Postoperative care

10.4

Postoperative treatment is given according to guidelines accepted in a centre. Main parameters of postoperative period are registered in patient's eCRF: admission and discharge dates (if the discharge is postponed for social reasons
‐ date, when patient was medically fit for discharge is documented), day of first bowel peristalsis, passing wind, opening bowels, start of fluids and soft diet, patients movement activity, blood transfusions. Complications are registered according to Clavien–Dindo classification. Treatment for complications is given according to local centre guidelines. Data on beginning, duration and treatment for complications is documented in patients' eCRF.

### Chemotherapy

10.5

Chemotherapy is given according to local guidelines and indications in the centre. Neoadjuvant chemotherapy is an exclusion criterion. After pathology report on removed specimen a decision on necessity of adjuvant treatment is made. As chemotherapy is given as a part of common treatment and is not a matter of research indications and contraindications (among them avoidance of pregnancy during treatment) are determined by a doctor prescribing chemotherapy according to current guidelines and recommendations. Data on all types of treatment is documented in eCRF.

### Follow‐up

10.6

Postoperative follow‐up includes investigations (CT chest and abdomen, colonoscopy) in 6 and 12 month, afterwards annually during the follow‐up period and examinations (or if in‐person contact is not possible it can be substituted by a phone call) in 30 days after surgery and afterwards every 3 month during follow‐up period. During follow‐up period complications, adjuvant treatment and recurrence are registered. Recurrence is registered when local recurrence or distant metastases are found during investigation (Colonoscopy, CT, MRI); serology recurrence is registered if CEA is 3 times higher than baseline. Quality of life will be assessed with validated questionnaires EORTC QLQ‐C30 and colorectal module CR 29 according to *Appendix*
S3 (supporting information).

Patients rejecting surgery after randomization or patients receiving different to randomization group treatment will be analysed in primary randomization groups. For patients rejecting treatment and follow‐up continuation of data collection without treatment is offered.

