### Randomization

7.2

Randomization will be performed via main centre (National Medical Research Centre of Oncology named after N.N. Petrov). Eligible patients will be randomized for D2 or D3 lymph node dissection in 1 : 1 ratio for D2 or D3 dissection according to computer generated randomization list created in beforehand^32^.

Information regarding restrictions of randomization to provide groups' homogeneity is located in the document “Mechanism of randomization in COLD trial”, kept in the main centre of the trial concealed from investigators enrolling patients.

Randomization will be performed via sending of randomization list (filled in after patient's enrolment) by electronic message to main centre, where patient will be assigned to a certain line in the randomization list. In reply message investigator receives randomization group and code of the line in the list.

There is no blinding of investigators or patients in current study.

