### Endpoints

7.3

Primary endpoint:
Overall survival (time frame: 5 years after last patient enrolment)

Secondary endpoints:
Disease‐free survival (local recurrence or distant metastases during study period)Short‐term outcomes (time frame: 30 days after operation)Lymph node metastasis pattern (number of lymph node with metastases related to number of lymph nodes studied in each lymph node group)CME quality (ratio of good, satisfactory and unsatisfactory quality)Lymph node yield (number of lymph nodes removed)Quality of life of patients

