## Follow‐up

12

Schedule of necessary investigations and follow‐up visits is in *Appendix*
S3 (supporting information).

Visit day date deviation: 30 day visit +/‐ 2 days, other visits ‐ +/‐ week. Data on completed visits is transferred to eCRF in 5 working days. Quality of life is assessed via questionnaires filled in before surgery, on day 30, 3‐month visit, 1, 3 and 5‐year visits.

To minimize number of patients lost for follow‐up patients are able to provide results of their routine follow‐up investigations and get a consult of expert centre, which will facilitate patients' adherence to follow‐up.

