## Sample size calculation and statistical analysis

15

To determine the sample size current data from national cancer registry was used^33^, according to which 5 year survival of colon cancer patients is 50%. Survey among surgeons revealed anticipated improvement of survival due to D3 lymph node dissection of 10%. For sample size calculation MedCalc software was used (function of sample size calculation for survival analysis (log rank test) using D. Machin method^34^), according to current survival data, sample size was determined as 762 patients. Using sample size calculation for superiority study via PASS software with C. Chow et al and J. Lachin et al method^35^, ^36^, with α – 0,05 and β – 80%, with 15% of patients lost for follow‐up in case of 3 year accrual period and 5 year follow‐up sample size was determined as 768 patients. As sample sizes obtained by different methods were similar the greater number was used to determine the sample size as 768 patients.

“Intent‐to‐treat” analysis will be performed, thus once randomized patients will be analysed in their randomization group, irrespective of actually received treatment.

For statistical analysis of primary endpoint (overall survival during the study period) Kaplan–Meier method will be implied as the probability of patients survival depends only on time after surgery, as there is no anticipated change of survival during the trial conduct. To compare survival curves long‐rank test will be used.

For secondary endpoints type of analysis will depend on the nature of data. For disease‐free survival (survival without local or distant recurrence during the study period) Kaplan–Meier curves will be used with the long‐rank test. For analysis of short‐term outcomes (morbidity and mortality), lymph node yield parametric and non‐parametric criteria will be used to compare mean values and contingency tables.

For categorical data, to assess the significance of association of two kinds of classification (contingency tables) exact Fisher's test will be implied by default as it can be used when sample distribution is only approximately equal to theoretical distribution and therefore this test is universal. For the final analysis as the sample reaches calculated size Pearson Chi square test will be used.

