Prior to comparing of group mean values in case of quantitative data, a non‐parametrical criterion of Shapiro Wilks will be used to test the normality of distribution. In case of normal distribution Student's criterion for independent samples will be used (dependant samples for quality of life assessment). For data not distributed normally non‐parametric Mann–Whitney U criterion will be implied.

Lymph node metastases pattern will be assessed as calculation of frequency of affected nodes related to number of studied nodes in each group. Correlation analysis of association of size, T‐stage, localization of the tumour with affected groups of lymph nodes, frequency of metastases, tumour budding grade, lymphovascular and perineural tumour invasion. Spearman rank correlation coefficient will be used as the data may be distributed not normally and numeric data may be included. To assess correlation of quantitative data distributed normally Pearson correlation coefficient will be implied.

For the primary endpoint and disease free survival missing data will be handled according to the survival analysis nature – censoring of the patient with the date of last contact.

Missing data for the secondary endpoints will be dealt with by using multiple imputations with Markov chain Monte Carlo method (monotone method if the data shows a monotone pattern of missing values; otherwise, fully conditional specification).

Conclusion of superiority of D3 lymph node dissection will be made in case of statistical superiority of survival during the study of D3 group over D2.

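### Overall survival is censored at last contact with no stated vital-status check at the cut-off, so deaths after loss (about 9% to 34% of those expected) go uncounted

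*Protocol article*

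**What the plan says.** All of this is in the protocol article.

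- Section 7.3 defines the primary endpoint as "Overall survival (time frame: 5 years after last patient enrolment".
- Section 10.6 sets contacts at 30 days after surgery and then every 3 months. If a patient cannot attend, "it can be substituted by a phone call". The items it lists for recording are complications, adjuvant therapy and recurrence; survival status is not among them.
- Section 10.6 keeps patients who decline surgery, or receive the other dissection, in their randomised group. For those who reject treatment and follow-up, "continuation of data collection without treatment is offered".
- Section 12 gives one measure against loss: "patients are able to provide results of their routine" investigations and obtain an expert-centre opinion.
- Section 15 treats missing data for overall and disease-free survival by "censoring of the patient with the date of last contact".
- Section 15 mentions a registry only as the source of the 50% control survival: "current data from national cancer registry was used".
- Section 7.2 states: "There is no blinding of investigators or patients in current study".
- On loss, section 15 says 15% of patients. The sample-size table (printed under section 13) uses a loss hazard of 0.165 a year in each arm.

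**The concern.** Overall survival does not need attendance. It needs a date of death, or the knowledge that the patient was alive on a given date. Under the stated rule a patient who stops attending leaves the risk set at the last contact, and a later death does not count unless it reaches the centre in some other way. The two measures that limit this, the offer of continued data collection and the option to send in outside results, both depend on the patient's willingness.

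Two things are at stake. The first is information: each unseen death is a lost primary event, and the log-rank test draws its power from events. The second is a possible bias. If one arm loses more patients than the other, and those lost have a worse prognosis than those who stay, censoring at last contact distorts the treatment contrast.

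**Working it through.** **Inputs.** Control 5-year survival of 50% and a gain of 10 points (section 15) give exponential hazards h1 = −ln(0.50)/5 = 0.1386 and h2 = −ln(0.60)/5 = 0.1022 a year, ratio 0.737; the table prints 0.139, 0.102 and 0.737. There are 384 patients per arm, uniform accrual over R = 3 years, and total duration T = 8 years. The loss hazard w is 0.165 a year (table) or, if 15% is read as cumulative over 5 years, −ln(0.85)/5 = 0.0325.

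**Formulas.** With s = h + w:

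- still under observation at study end: A = (e^(−5s) − e^(−8s)) / (3s)
- death observed: P = (h/s)(1 − A)
- lost before death or study end: L = (w/s)(1 − A)
- power = Φ( (h1 − h2)/√((v1 + v2)/384) − z ), with v = h²/P

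**The plan's own figure, w = 0.165.**

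- D2: s = 0.3036, A = 0.1438, P = 0.3909, so 384 × 0.3909 = 150.1 deaths.
- D3: s = 0.2672, A = 0.1809, P = 0.3132, so 384 × 0.3132 = 120.3 deaths.
- The total is 270.4, with variances 0.0492 and 0.0333. The table prints 150, 120, 270, 0.049 and 0.033.
- Power with one-sided α = 0.05: 0.03646/√(0.08248/384) = 2.488; 2.488 − 1.645 = 0.843; Φ = 0.800. The table prints 0.8004.
- The table is therefore reproduced, and it is a one-sided calculation. The text gives only "with α – 0,05 and β – 80" percent and no sidedness.
- Lost before death or study end: 46.5% of D2 and 50.6% of D3.

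**Complete vital status, w = 0.**

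- P = 0.5909 and 0.4832, so 226.9 + 185.6 = 412.5 deaths.
- One-sided power: 0.03646/√(0.05412/384) = 3.071; less 1.645 = 1.427; Φ = 0.923.

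**15% lost over 5 years, w = 0.0325.**

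- P = 0.5408 and 0.4403, so 207.7 + 169.1 = 376.8 deaths. Lost: 12.7% and 14.0%.
- One-sided power: 0.03646/√(0.05924/384) = 2.936; less 1.645 = 1.291; Φ = 0.902.

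**Comparison.**

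| Loss | Deaths seen | Unseen | Share unseen | Power, one-sided | Power, two-sided |
|---|---|---|---|---|---|
| 0.165 a year | 270 | 142 | 142.1/412.5 = 34% | 0.80 | 0.70 |
| 15% over 5 years | 377 | 36 | 35.7/412.5 = 9% | 0.90 | 0.84 |
| none | 412 | 0 | 0% | 0.92 | 0.87 |

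The 142 unseen deaths divide as 77 in D2 and 65 in D3. These counts assume the same death hazard after loss as before it.

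**Effect on the treatment contrast.** This part is simulated and rests on assumptions that are not in the documents.

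- Equal loss in both arms, mortality doubling after loss: the hazard ratio with censoring differs from that with complete follow-up by about 0.01 or less at either loss rate, and stays at 1.00 under the null.
- 30% frail patients with 3 times the death hazard and 4 times the loss hazard, no treatment effect: equal loss leaves the ratio of death rates at 1.00. With more loss in D3 (0.045 against 0.02 a year, or 0.20 against 0.13) it moves to about 0.98, in favour of D3.

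**The case against.** The strongest reply is that nothing here departs from usual practice. Last-contact censoring is a standard rule for patients who cannot be traced. Continued data collection can only be offered, never imposed, so that sentence is itself a safeguard; phone contact and the retention measure add to it. Section 14 names inpatient and outpatient files as data sources, so visits and calls are not shown to be the only route to a date of death. An article also condenses: tracing may be described in the full protocol, the follow-up appendix or the analysis plan. Finally, the sample size already allows for loss, since 270 events give the planned 0.80 power.

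Much of this stands, and it rules out several stronger readings that a reader might infer:

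- **Deaths counted asymmetrically.** One might suppose that a relative's later report becomes an event while a lost survivor is cut back to the last contact. The documents do not say how late reports are treated, and they give no reporting rate.
- **Large bias in the result.** Informative loss can shift the survival estimate of a single arm noticeably, but the primary analysis compares arms. Under the equal loss that the table assumes, the shifts nearly cancel.
- **Vital status known to be obtainable.** The registry is cited for an aggregate survival rate; individual access is not mentioned.
- **No contacts for patients who decline surgery.** The 30-day contact is dated from surgery, but these patients may have a schedule in the appendix that is not shown.

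What the reply does not remove is that the article fixes the censoring rule for the primary endpoint and sets no step before it to find out whether the patient is alive. Budgeting for lost events does not make it sensible to leave recoverable ones uncounted.

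**Conclusion.** The point holds as a worthwhile improvement to the handling of the primary endpoint; it does not show that the trial's result will be biased. As written, deaths after loss go uncounted: about 36 of 412 (9%) if 15% are lost over 5 years, and about 142 of 412 (34%) at the table's loss hazard of 0.165 a year. The two loss figures do not agree if 15% is cumulative, because 0.165 a year means 1 − e^(−0.825) = 56% lost over 5 years, so the cost is given as a range. Complete status would raise one-sided power from 0.80 to 0.92 at the table's hazard, or from 0.90 to 0.92 at the lower one. These gains are upper limits, because some patients will refuse or remain untraceable.

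The sizes rest on the plan's exponential hazards, equal loss in both arms and unchanged mortality after loss. Bias in the hazard ratio would require loss that differs by arm and is tied to prognosis. The absence of blinding makes this possible, but nothing in the documents shows it.

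**What to change.** In sections 10.6 and 15:

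1. Distinguish refusal of treatment or visits from refusal of vital-status follow-up, and record each separately.
2. Set one fixed data cut-off. At that date each centre establishes alive or dead, with the date, for every randomised patient, including those who declined surgery or visits. Both arms are searched by the same method and with the same effort.
3. Name the sources: medical files, a phone call and, where access and consent allow, registry or civil records. That patient-level access exists is an assumption and needs checking.
4. Censor patients known to be alive at the cut-off on that date. Keep last-contact censoring only where status cannot be established or the patient refuses, and report the number of such patients by arm.

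If an unseen document already provides for this, a cross-reference in section 15 is enough.

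The cost is a short paragraph in the protocol, a line of consent wording, and one status query for each patient out of contact at the cut-off. No extra visits, procedures or patients are needed. The downside is modest administrative work, and some patients will still be untraceable.
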